### Storage and distribution

GPA and creatine capsules will be stored at room temperature. The participants will receive the test products at the hospital and will be instructed to store the capsules at room temperature at home.

The test products will be labeled with a study number, with the pharmacy holding the key to the content until the end of the data collection.

### Dose calculation

For GPA, we used the FDA guidance on Estimating the Maximum Safe Starting Dose in Initial Clinical Trials in Adult Healthy Volunteers [29]. This guidance outlines a process for deriving the maximum recommended starting dose for first-in-human clinical trials in adult healthy volunteers, and recommends a standardized process by which the maximum recommended starting dose can be selected. The purpose of this process is to ensure the safety of the human volunteers [29]. Toxicity should be avoided at the initial clinical dose. However, doses should be chosen that allow reasonably rapid attainment of phase 1 trial objectives [29]. The major elements of this process are as follows:Determination of the no observed adverse effect levels (NOAELs) in the tested animal speciesConversion of NOAELs to human equivalent doses (HED)Application of a safety factor.

### 1. No observed adverse effect level (NOAEL) determination

In animal studies, GPA was administered through the diet in concentrations of 1% or more over 8 weeks without apparent adverse effects [16]. In animals weighing 200 grams eating 20 grams per day, we calculated a 'no observed adverse effect level' of 1,000 mg/kg/day.

Furthermore, in a patent application, Meglasson *et al*. recommended a human dose of 1 to 500 mg/kg/day based on his research in mice and rhesus monkeys [30]. In this paper, rhesus monkeys weighing 9 kg were treated with oral GPA 48 mg/kg/day (432 mg per monkey per day) over 2 weeks without apparent adverse events.

### 2. Conversion of the no observed adverse effect level (NOAEL) to human equivalent dose (HED)

We converted the oral NOAELs in rats and monkeys (resp. 1,000 mg/kg/day and 48 mg/kg/day) to oral HEDs based on an algorithm proposed by the FDA based on body surface area [29]. This algorithm proposes a conversion factor from rat to human of 0.16 times the rat dose; and of monkey to men of 0.32 the monkey dose (in mg/kg/day; for a man of 60 kg) resulting in HEDs of resp. 160 mg/kg/day and 15 mg/kg/day for a man of 60 kg.

### 3. Application of a safety factor

A safety factor should be applied to the HED to increase assurance that the first dose in humans will not cause adverse effects. The use of the safety factor is based on the possibility that humans may be more sensitive to the toxic effects of a substance than predicted by the animal models, that bioavailability may vary across species, and that the models tested do not evaluate all possible human toxicities, or cannot be expressed by animals or easily measured, such as headache or nausea. We conservatively chose 15 mg/kg/day oral dose for our final calculations of the human dose, because this is the lowest dose, and because of the closer allometric relationship between monkey and man [29]. FDA advises a safety factor of at least 10. Based on an average weight of a male volunteer of 75 kg, we calculated a starting oral dose for this phase 1 study of 75*1.5 mg/day = 112.5 mg/day; we will use 100 mg/day.

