### Eligibility

We will include healthy men aged 18 to 50 years, with a normal, nonobese body mass (BMI 18.5 to 29.9 kg/m^2^). Exclusion criteria include high blood pressure or the use of antihypertensive drugs at baseline, (history of) cardiovascular disease including TIA and stroke; the use of plasma CK-increasing drugs including statins; use of acetylsalicylic acid or nonsteroidal anti-inflammatory drugs in the two weeks prior to the first visit; neuromuscular or endocrine disorders; vasculitis; HIV infection; infectious hepatitis; personal or family history of bleeding disorders; sickle cell anemia or other hereditary anemia; smoking; current use or use within two months prior to start of the trial of beta-guanidinopropionic acid or creatine; and abnormalities in glucose, lipid spectrum, thyroid, kidney, or liver biochemistry parameters in the plasma. To stabilize and standardize plasma CK activity during the trial, participants are instructed not to perform exercise three days prior to the baseline visit or during the intervention in the first week [6].

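### At a flat 100 mg/day, the adopted safety factor of at least 10 on the monkey-based human equivalent dose is met only at or above about 65 to 67 kg, and the eligibility criteria shown admit lighter men

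*Protocol article*

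**What the plan says.** The protocol article derives the GPA dose in three steps.

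- *NOAEL determination.* One source is a patent application in which "rhesus monkeys weighing 9 kg were treated with oral GPA 48 mg/kg/day (432 mg per monkey per day) over 2 weeks". A second value, 1,000 mg/kg/day, comes from animals fed GPA in the diet and is treated as the rat value in the next step.
- *Conversion to HED.* The monkey factor is given as "of monkey to men of 0.32 the monkey dose (in mg/kg/day; for a man of 60 kg", and the two conversions are reported as "resulting in HEDs of resp. 160 mg/kg/day and 15 mg/kg/day for a man of 60 kg".
- *Application of a safety factor.* The lower HED is selected: "We conservatively chose 15 mg/kg/day oral dose for our final calculations of the human dose, because this is the lowest dose". The minimum margin is then cited: "FDA advises a safety factor of at least 10". The dose follows: "Based on an average weight of a male volunteer of 75 kg, we calculated a starting oral dose for this phase 1 study", with the result "75*1.5 mg/day = 112.5 mg/day; we will use 100 mg/day".

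The Study design section assigns 100 mg to everyone in the GPA arm and mentions no adjustment for weight. The Eligibility section limits body size only through BMI: "with a normal, nonobese body mass (BMI 18.5 to 29.9 kg/m^2". No minimum body weight appears among the criteria listed.

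**The concern.** The HED and the safety factor are both on a mg/kg scale, whereas the dose is a fixed number of milligrams. Converting at one weight gives the intended mg/kg dose only at that weight. Lighter men receive more mg/kg and so have a smaller margin to the HED. The factor is cited as a minimum, the HED is stated for a 60 kg man, and the conversion uses 75 kg. The article does not say what margin applies at any other weight.

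This matters because the trial is a first-in-man study with tolerability as its primary outcome, and the Discussion presents the low dose as the means of preventing toxicity. A safety margin that supports such an argument should be stated correctly for all the men who may be dosed.

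**Working it through.** **Inputs, all from the protocol article**

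- Monkey NOAEL 48 mg/kg/day; conversion factor 0.32 (NOAEL and HED sections).
- HED used 15 mg/kg/day; safety factor 10; conversion weight 75 kg; dose 100 mg/day (safety-factor section).
- BMI 18.5 to 29.9 kg/m² (Eligibility).

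**Step 1: reproduce the article's figure**

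- HED = 48 × 0.32 = 15.36, reported as 15 mg/kg/day.
- 15 / 10 = 1.5 mg/kg/day.
- 1.5 × 75 = 112.5 mg/day, lowered to 100 mg/day. This matches exactly.

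**Step 2: margin delivered by the flat dose**

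Factor at weight W = HED × W / 100.

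| Weight (kg) | mg/kg/day received | Factor, HED 15 | Factor, HED 15.36 |
|---|---|---|---|
| 75 | 1.33 | 11.25 | 11.52 |
| 70 | 1.43 | 10.5 | 10.75 |
| 65 | 1.54 | 9.75 | 9.98 |
| 60 | 1.67 | 9.0 | 9.2 |
| 55 | 1.82 | 8.25 | 8.45 |

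**Step 3: weight at which the factor is exactly 10**

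W = 100 / (HED / 10).

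- HED 15: 100 / 1.5 = 66.7 kg.
- HED 15.36: 100 / 1.536 = 65.1 kg.

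At 60 kg, HED/10 corresponds to 15 × 60 / 10 = 90 mg (92.2 mg unrounded), against the 100 mg given.

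**Step 4: does the BMI range admit such weights?**

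Lowest admitted weight = 18.5 × height². BMI at which the factor is 10 = 66.7 / height². Both factor-based columns use HED 15.

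| Height (m) | Lowest admitted weight (kg) | Factor there | Eligible BMI below which the factor is under 10 |
|---|---|---|---|
| 1.70 | 53.5 | 8.0 | 23.1 |
| 1.75 | 56.7 | 8.5 | 21.8 |
| 1.80 | 59.9 | 9.0 | 20.6 |

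At BMI 18.5 the weight reaches 66.7 kg only at √(66.7 / 18.5) = 1.90 m. Any shorter man therefore has some eligible weight at which the factor is below 10.

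**Step 5: sensitivity (an assumption, not in the article)**

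Suppose the total HED scales with body surface area around 60 kg, that is, with weight to the power 0.67. The break-even weight is then 60 × (1000 / (HED × 60))^(1/0.67), which is about 70.2 kg for HED 15 and 67.8 kg for HED 15.36. The conclusion does not weaken under this scaling.

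**The case against.** The case on the other side has real force.

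- *Nothing is miscalculated, and the basis is disclosed.* This stands. The article says openly that it used an average weight, and at that weight the margin is above 10. It gives no explicit guarantee for each volunteer. But the factor is cited as a minimum and is applied as exactly 10 in the 1.5 mg/kg step, so a reader will take it as met for those dosed.
- *Lowering 112.5 to 100 mg gives cover below the average.* This also stands. It moves the break-even weight from 75 kg to about 67 kg, and every man at or above that weight keeps a factor of at least 10. It does not reach 60 kg.
- *The basis is the stricter of two.* On the rat HED the factor at 60 kg is 160 × 60 / 100 = 96. That is useful context, but the article chose the monkey value expressly because it was the lower, so the margin has to be judged on it.
- *The full protocol may contain a weight criterion.* This is possible. The exclusion list is introduced in a way that does not claim completeness, and the article condenses an approved protocol. If a criterion exists there, citing it would settle the point.

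A reader might go further and infer that lighter volunteers are exposed to a toxic dose, or that only men close to 75 kg are protected. The documents support neither. The monkey value is a dose given without apparent adverse events, not a toxic threshold, and the margin rises with weight above 67 kg.

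**Conclusion.** The point holds in a limited form. The dose calculation is correct, but the adopted minimum factor of 10 is met only at or above about 67 kg (65 kg with the unrounded HED). It is 9.0 (9.2 unrounded) at the 60 kg for which the HED is stated, and roughly 8.0 to 8.5 at the bottom of the BMI range for men of 1.70 to 1.75 m.

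The shortfall is modest. How many of the eight GPA recipients it would affect cannot be computed, because the article gives no weight distribution. The conclusion assumes that the HED applies per kilogram, as the article itself uses it, and that no weight criterion exists beyond those listed. No comparison, sample size or analysis is altered. This is an inaccuracy in a stated safety margin that is worth correcting, but it is not a defect that undermines the trial.

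**What to change.** The sponsor should reconcile four places in the protocol article: the conversion to HED, the application of the safety factor, the flat dose in Study design, and the body-size criterion in Eligibility. The safety-factor section should state the margin actually delivered across the admissible weight range, not only at the 75 kg average. If the full protocol sets a weight criterion, the section should cite it instead. Which element changes, if any, is for the sponsor's clinical team; no dose or weight limit is proposed here.

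Optionally, each volunteer's mg/kg dose can be reported beside the adverse events. The Quality control section already provides for standardised measurement of weight, so this needs no new data.

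The cost is a short text amendment and no additional participants. The downside is that the stated margin becomes slightly less favourable at low weights.

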### Creatine

Creatine, which has an identical molecular formula as GPA, was chosen to simultaneously assess the effect of the synergist on peripheral hemodynamics. The average daily rate of creatine synthesis in healthy omnivorous males is estimated to be 1.3 g [31]. We will use 5 g as recommended in studies on creatine supplementation. No side effects are apparent at this dose [31,32].

### Study design

We wrote the protocol using the SPIRIT '(Standard Protocol Items: Recommendations for Interventional Trials)' recommendations and the 'Template for Intervention Description and Replication (TIDieR) checklist' [33,34].

The ABC trial is a randomized, placebo and active controlled, double-dummy, participant, intervention provider, and outcome assessor (triple) blinded, parallel group, single center (Academic Hospital of the University of Amsterdam), exploratory trial, with three arms: a primary outcome of tolerability of GPA, in comparison with creatine and placebo.

Randomization will be performed by an independent party, the Clinical Pharmacy Unit of the Academic Hospital of the University of Amsterdam, using a computer-generated, nonadaptive, and restricted randomization scheme and a 1:1:1 allocation ratio. The Pharmacy will generate the random allocation sequence. All participants who give consent for participation and who fulfill the inclusion criteria will be randomized to receive GPA 100 mg and creatine placebo matching active creatine 5 gram; creatine 5 gram and GPA placebo matching GPA 100 mg; or double dummy placebo over 1 week. The participant will receive the blinded, randomized trial supplements from the pharmacy. Allocation concealment will be ensured, as the pharmacy will store the allocation list and not release the randomization code until all outcome measures have been assessed and the data bank has been closed. Thus, randomization will be conducted without any influence of the investigators, outcome assessors, or participant characteristics. After assignment to interventions, trial participants, trial staff, and the outcome assessor will remain blinded to whether the participant was given a placebo or a supplement until after all outcome data have been assessed. Data analysis will be performed unblinded. We prespecified the use of accumulating data to decide whether to stop the trial early, in case of serious or unexpected side effects. Independent monitoring visits will take place before the start of the trial, within 1 month after initiation or after inclusion 5th subject; within 2 months after initiation or after inclusion 15th subject; after last patient last visit; and after the data have been entered into the database. Data entry will be verified by two independent researchers. Budget administration is by an independent organization (AMC Research BV, Amsterdam, the Netherlands).

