### Adverse and serious adverse events

We do not expect any adverse effects from this low dose study. There are no FDA or other reports in formal or informal sources on the side effects of ingestion of this dose of GPA or creatine in animals or humans. Therefore, a 1-day first-in-men study that we had proposed, with hourly observation and physical and laboratory examination of the subjects, was deemed unnecessary by the MERC. Subjects with hypertension, a history of cardiovascular, liver, or kidney disease, or with laboratory abnormalities at baseline will be excluded. Adverse events reported by the included subject spontaneously or through the questionnaire, or observed by the trial staff or health care worker, will be recorded and judged by the study group and the independent physician. The trial staff will convert reported symptoms to a standard lexicon, the Common Terminology Criteria for Adverse Events (CTCAE) [37], to facilitate international scientific reporting. Adverse effects will be classified based on the FDA guideline [29], as overt toxicity (for example, clinical signs, macro- and microscopic lesions); surrogate markers of toxicity (for example, plasma liver enzyme levels); or other adverse effects. The ADR probability scale [38] will be used to assess the causal relationship between trial supplement use and any reported adverse event. Adverse events will be followed until they have abated, or until a stable situation has been reached. Depending on the event, follow-up may require additional tests or medical procedures.

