### Quality control

We will ensure that quality controls will be executed throughout the conduct of the study, with regard to participant selection, data collection, data processing and reporting. Additionally, trial staff who collect the data will be well-trained according to standard operating procedures, in the study requirements, use of the questionnaire, counseling for adherence, standardized measurement of height, weight, brachial blood pressure, electrocardiography and noninvasive hemodynamics, as well as for requirements for laboratory specimen collection including morning urine samples. On every day of the data collection, we will monitor and ascertain the performance of our measurement devices. Our database was designed to allow checks on the completeness of the entered data and basic data checks, and we will use independent double data-entry followed by matching and checking for data-entry errors. Data cleaning will be performed according to expert consensus. Finally, we will check internal and external consistency of the analyzed data before writing reports.

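### The article gives three different end points for blinding, and only one waits for the data bank to close; align them, and use coded labels for the main outputs

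*Protocol article*

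**What the plan says.** Three statements in the protocol article bear on when the allocation may become known.

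- Storage and distribution: products carry a study number, "with the pharmacy holding the key to the content until the end of the data collection".
- Study design, on allocation concealment: the pharmacy will "not release the randomization code until all outcome measures have been assessed and the data bank has been closed".
- Study design, on participants, trial staff and the outcome assessor: they "will remain blinded to whether the participant was given a placebo or a supplement until after all outcome data have been assessed".

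Study design then adds: "Data analysis will be performed unblinded". The same section describes the trial as "participant, intervention provider, and outcome assessor (triple) blinded".

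The steps that turn raw reports into results are described elsewhere. Under Adverse and serious adverse events, reported events "will be recorded and judged by the study group and the independent physician", trial staff translate symptoms into CTCAE terms, and causality is scored on an ADR probability scale. Under Quality control there is double entry with matching, then "Data cleaning will be performed according to expert consensus", and at the end: "Finally, we will check internal and external consistency of the analyzed data before writing reports". Neither section places these steps before or after code release.

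**The concern.** The primary outcome is tolerability of GPA against placebo, reported descriptively. It rests largely on questionnaire answers (check boxes and free text) that staff code by hand and that the study group and an independent physician judge. The authors also say in advance that they expect no adverse effects and no difference between arms. In that setting, coding, causality scoring and consensus cleaning are the steps most open to influence from knowledge of the arm.

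The article is meant to settle when that knowledge becomes available, and it gives more than one answer. A pharmacy or monitor working from the storage section could release the key earlier than the study design section allows. The planned unblinded analysis means there is no second barrier once the code is out.

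**Working it through.** No arithmetic applies, and the article states no figure to reproduce. The check is to set the statements side by side and ask what each permits.

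**1. The release times differ.**

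| Place | Event that ends the restriction | Waits for data bank closure? |
|---|---|---|
| Storage and distribution | Data collection ends | No |
| Study design, allocation concealment | Outcomes assessed and data bank closed | Yes |
| Study design, staff and assessor blinding | Outcome data assessed | Not mentioned |

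All three are current text, and none is said to override the others.

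**2. The end of collection and closure are not the same moment.** Study design schedules one monitoring visit after the last participant's last visit and another after data entry. Quality control adds matching, error checks and cleaning. Some work can therefore remain after the last observation, the Day 21 tolerability assessment.

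**3. What each rule would expose.**

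- *Storage rule:* any CTCAE coding, causality scoring or cleaning still open when collection ends could be finished with the arm known.
- *Allocation concealment rule:* tolerability is the primary outcome, so judging adverse events is part of assessing outcomes and comes before release. Cleaning is covered if it is finished before closure.
- *Staff-blinding sentence:* adverse event judgement is covered as outcome assessment. Cleaning is not clearly covered, because closure is not named.

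**4. Unblinded analysis.** The article defines triple blinding as participant, intervention provider and outcome assessor. The analyst is not in that list, so an unblinded analysis is consistent with the definition. Knowledge of the arm can affect analysis choices only where they are not already fixed. A statistical analysis plan may fix them, but it is not shown.

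**5. Would coded labels work?** Laboratory studies measures GPA and creatine in plasma and 24-hour urine at baseline and after 1 and 7 days. With one arm taking GPA and another taking 5 g of creatine, those results would probably identify the arms behind the labels A, B and C. Labels help only if these results are kept apart until the other outputs are final.

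**6. A possible fourth time, ruled out.** Handling and storage of data and documents mentions a key held by the clinical project leader. This appears to be the participant identification code, not the randomization code, so it is not counted.

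**The case against.** The strongest reply is that the allocation concealment rule is the explicit and detailed one, placed where a reader would look for it, whereas the storage clause is a passing remark in a paragraph on labelling. Under the detailed rule, adverse event judgement is already protected, and so is cleaning done before closure. Unblinded analysis is openly declared and fits the article's own definition of triple blinding. The hemodynamic measures are recorded by devices, and no mechanism is shown by which release after closure would alter them. All of this stands, and it limits the point to reconciling text and adding an inexpensive safeguard.

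A reader might infer more than the article supports in four ways.

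- *That all coding and cleaning fall between the two release times.* No section says so. Events are judged and followed until they abate, and the safety sections call for action during the study, so much of the judgement probably happens while everyone is blinded.
- *That the closing consistency check lets closed data be changed with the arm known.* Quality control plans a check of analyzed data before reporting; it does not say that closed data may be altered.
- *That one reclassified volunteer out of eight, 1/8 = 12.5 percentage points, measures the bias.* That is only the granularity of an arm of eight and is the same under perfect blinding.
- *That the outcome is purely subjective.* An independent physician, a standard lexicon, a causality scale and laboratory markers of toxicity are also named.

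The reply does not remove the differing statements. A detailed rule in one section does not stop someone acting on the looser one in another.

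**Conclusion.** The point holds as an inconsistency that should be reconciled. The storage section and the study design section give different release times, and the staff-blinding sentence omits closure. Exposure of adverse event coding, causality scoring and cleaning is conditional: it arises if the storage wording is followed while those steps are unfinished, or, for cleaning, if it is not complete before release. The article does not show that this will happen. The unblinded analysis is not an error or a contradiction; it is a safeguard forgone.

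No numerical size can be attached, because the article gives no test, threshold or expected event rate from which a bias could be computed. The practical weight comes from a primary outcome that is coded and judged by people, in arms of eight. The conclusion assumes that the full protocol or an analysis plan, neither of which is shown, does not already settle the release time. If one does, the article's wording still needs to match it.

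**What to change.** 1. Give one release time in Storage and distribution and in both Study design sentences: the code is released, and staff blinding ends, only after adverse event coding, causality scoring and data cleaning are complete and the data bank is closed. The separate emergency unblinding provision is unaffected.
2. Replace the statement on unblinded analysis. The tolerability and hemodynamic outputs are produced under labels A, B and C supplied by the pharmacy, and the arm names are revealed once those outputs are final.
3. Withhold plasma and urine GPA and creatine results from the analyst until then, since they would probably reveal the arms.
4. Log any data correction made after closure, with its reason and whether the arm was known.

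Item 1 is wording only. Items 2 to 4 need slightly more handling; the pharmacy already holds the allocation list and can supply the labels. The label blinding will be imperfect, because other data may hint at the arm. It is an added safeguard and does not replace item 1.
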